### Descriptive analyses

Descriptive data analyses will be carried out on the study cohort.^30,31^ We will describe the baseline demographics and characteristics of the patients with HF including the distributions of age, gender, ethnicity and IMD, and the prevalence of comorbidities and medication use at baseline, i.e. at HF diagnosis. We will also describe the temporal prevalence of HF across the GP practices involved in the study and assess the baseline distributions of serum creatinine and eGFR within various strata.

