### Participants

The study population will consist of all patients with their first ever recorded diagnosis of HF between 1 January 2005 to 1 March 2022. We chose to use data after 2005 as the Quality and Outcomes Framework (QOF) was introduced in UK general practices in 2004 and resulted in improved recording in medical records of long-term conditions in primary care. All registered patients with a first Read v2 or SNOMED CT code for HF during the study period will be included in the study population. The clinical code lists will be made available in the GitHub repository: https://github.com/alxv/Renal-HF.

There will be no restrictions to location in terms of the population sampled. A patient’s follow-up will commence on their index (onset of HF) date and terminate on either the last date of data collection (at the practice-level), the date that they transferred out of the practice, their date of death, or the end of the study, whichever happens first. Patients will be excluded from the study if they have had a history of renal replacement therapy (dialysis, filtration, or transplant) prior to their HF diagnosis. Patients who die or are lost to follow-up before the first valid serum creatinine (t_0_) is measured are excluded from longitudinal analysis as it is not possible to determine baseline renal function. A flow diagram of criteria for inclusion/exclusion is presented in *Figure 2*.

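### HF prevalence over time is to be described on a cohort of first diagnoses from 2005, so the series starts near zero and its early rise is an artefact

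*Protocol article*

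**What the plan says.** The section Descriptive analyses names both the data and the quantity. On the data: "Descriptive data analyses will be carried out on the study cohort". On the quantity: "We will also describe the temporal prevalence of HF across the GP practices involved in the study".

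The section Participants defines the cohort: "The study population will consist of all patients with their first ever recorded diagnosis of HF between 1 January 2005 to 1 March 2022". It repeats the entry rule: "All registered patients with a first Read v2 or SNOMED CT code for HF during the study period will be included in the study population". Each patient's time starts at HF onset: "follow-up will commence on their index (onset of HF) date and terminate on either the last date of data collection". One exclusion also bears on the count: "Patients will be excluded from the study if they have had a history of renal replacement therapy", meaning therapy before the HF diagnosis.

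The reason given for the 2005 start is recording quality: "We chose to use data after 2005 as the Quality and Outcomes Framework (QOF) was introduced in UK general practices in 2004". The article does not describe a separate extract of existing HF cases, or a registered-population denominator, for this description.

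**The concern.** Prevalence on a given date counts everyone living with the condition then, whenever it was diagnosed. The cohort is an inception cohort: it admits new cases from 1 January 2005 and nobody diagnosed earlier. The named data set therefore cannot supply the numerator of the named quantity in the early years. It also holds no one without HF, so the denominator has to come from outside it. Adding practice list sizes would supply that denominator but would not restore the missing cases.

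What is at stake is a reported result about the burden of HF. The abstract opens by calling HF a growing problem, so a rising curve would look like confirmation and might go unquestioned, although its early part would only show the cohort filling up.

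**Working it through.** The documents state no figure for HF prevalence, so there is nothing to reproduce. The 25% outcome prevalence under Sample size concerns the model outcome, not HF.

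**Inputs from the documents.** The window runs from 1 January 2005 to 1 March 2022, about 17.16 years. Entry is at first HF diagnosis. Exit is at death, transfer out, last data collection or study end.

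**Assumptions, not in the documents.** Incidence I is constant, and so is the exit rate m (death plus transfer out). The median time from diagnosis to exit is taken as 2 to 10 years. Since m = ln 2 / median, m runs from 0.693/10 = 0.07 to 0.693/2 = 0.35 per year.

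**Formula.** The true steady-state pool of living cases is I/m. The pool made up only of diagnoses since the window opened is (I/m)(1 − exp(−mt)) after t years. The share captured is therefore 1 − exp(−mt). At t = 0 this is 0 whatever m is.

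**Example.** With a median of 5 years, m = 0.693/5 = 0.139. After 5 years the share is 1 − exp(−0.693) = 50%.

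| Assumed median time to exit (years) | 1 year | 5 years | 10 years | 1 March 2022 | Years to reach 95% |
|---|---|---|---|---|---|
| 2 | 29% | 82% | 97% | 99.7% | 8.6 |
| 3 | 21% | 69% | 90% | 98% | 13.0 |
| 5 | 13% | 50% | 75% | 91% | 21.6 |
| 8 | 8% | 35% | 58% | 77% | 34.6 |
| 10 | 7% | 29% | 50% | 70% | 43.2 |

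**Apparent increase when the truth is flat.** From year 1 to March 2022 the ratio is 0.997/0.293 = 3.4 for a median of 2 years, 0.907/0.129 = 7.0 for 5 years and 0.696/0.067 = 10.4 for 10 years. From year 5 it is much smaller: 0.997/0.823 = 1.2, 0.907/0.500 = 1.8 and 0.696/0.293 = 2.4. Most of the distortion lies in the first years.

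**If incidence falls.** With incidence changing as exp(gt), the cohort pool is proportional to (exp(gt) − exp(−mt))/(m + g). For g = −0.03 or −0.05 and medians of 3, 5 or 10 years, the pool still rises at first. It peaks between about mid-2013 (median 3 years, g = −0.05) and the end of the window (median 10 years, g = −0.03). After a peak inside the window it declines.

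**Counting all living cases.** If diagnoses before 2005 are included, the captured share is 100% in every year, and the curve is flat when incidence and exit are constant.

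**The case against.** The strongest reply is that the sentence is underspecified rather than wrong. Read strictly, the cohort gives no prevalence at all, because it has no people without HF. The sentence also refers to the participating practices, so some data from outside the cohort must be meant, and the numerator might come from there too. To establish that a diagnosis is the first ever, someone must look for earlier HF codes, so pre-2005 cases may be identifiable. The article condenses a fuller protocol, and the authors may simply have meant yearly new diagnoses.

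Part of this stands. A reader might infer that the source database cannot yield HF prevalence. The documents do not support that: a wider extract could well do so. Nor is the artefact certain under every way of carrying out the sentence; it follows when the cohort supplies the numerator. But that is the data set the section names, and the article describes no other. This is a stated source that does not fit a stated quantity, not just an omitted detail. If new diagnoses were meant, the word should be incidence.

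It is also fair to say that the size rests on an assumed exit rate, and that nothing else in the study uses this output.

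**Conclusion.** The point holds for the early years of the series. With the study cohort as numerator, HF prevalence is near zero at the start of 2005 under any assumption, and the first part of the curve shows the cohort filling. Under constant incidence and an assumed exit rate of 0.07 to 0.35 per year, 7–29% of true prevalence is captured after 1 year, 29–82% after 5 years and 70–99.7% by March 2022. The exclusion for earlier renal replacement therapy removes further living cases; the documents give no means of saying how many.

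Three stronger readings are not supported:

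- **That the series must rise throughout.** It levels off, and can fall if incidence falls. How long the artefact lasts depends on the exit rate.
- **That differences between practices would reflect when each practice's data begin.** The article gives no practice start dates and does not say that they vary.
- **That the prediction work is compromised.** The primary endpoint, sample size, models, validation and model selection do not draw on this description.

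The sentence should be corrected because it fixes a misleading reported result and is easily repaired. The consequence is confined to that one output.

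**What to change.** Choose one of two changes to the sentence in Descriptive analyses.

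1. **Report incidence.** Replace temporal prevalence with the annual incidence of first HF diagnosis per registered person-years, by practice and calendar year. The cohort supplies the new diagnoses; the person-time must come from the wider database. Either lift the renal replacement exclusion for this table or state that it applies.
2. **Keep prevalence, but change the numerator.** For this table only, count all registered patients with any HF code on or before each mid-year date, including codes before 2005, over all registered patients on that date. State that this count is not restricted to the study cohort.

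The cost is one sentence, plus registered-population denominators and, for the second option, a count of existing cases from the wider database. Nothing changes in the prediction models, the sample size or the validation.

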### Prediction models

To predict serum creatinine trends, we will perform and compare three different modelling strategies. Modelling a continuous trajectory allows us to capture the rate of decline and dynamically recalculate the risk of WRF in relation to the change in baseline patient. This approach offers greater clinical utility than binary classification alone.

**Mixed-effects model**: The longitudinal component is based on a linear mixed-effects regression model. Variable selection is done with the least-absorption and selection operator (LASSO) to avoid overfitting by penalizing regression coefficients.
**Growth mixture model:** GMM is used to identify latent subgroups (classes) of a population that follow different growth trajectories. To mitigate overfitting in the GMM, the optimal number of latent classes (K) will be determined using the Bayesian information criterion and Akaike information criterion, with a minimum class size constraint enforced to ensure generalizability.
**RNN-LSTM:** Deep learning model using LSTM will be developed to handle complex nonlinear time dependencies. The model architecture consists of two LSTM layers (64 units each) with a dense output layer. To address the specific data requirements of neural nets, continuous variables (e.g. creatinine, urea) will be log transformed or standardized to ensure effective optimization, while clinical scales will be used in statistical models. To meet the specific data requirements of ML models, the continuous variable log transformation or standardization will be performed. Overfitting in RNN-LSTM is mitigated by early stopping, where training is stopped when the validation loss does not improve after a certain number of epochs (patience), in combination with drop-out regularization layers.

### Statistical modelling

The longitudinal component will consist of a linear mixed-effects regression model for the repeated measures of serum creatinine (at the patient level). To select variables for inclusion in the longitudinal sub model, we will use the LASSO proposed by Tibshirani (1996) which is based on penalized regression and uses an *L*_1_-penalty on the regression coefficients.^32^ Selection will be undertaken using a Gaussian link function in the R package glmmLasso which combines gradient ascent optimization with the Fisher scoring algorithm^33^. The mixed effects model (incorporating those variables selected via the LASSO) will be estimated using the R package nlme—as this provides the requisite outputs to be applied as arguments in the subsequent joint modelling phase. A GMM is a type of finite mixture model that assumes different subgroups (classes) in the population follow different growth trajectories. It combines features of growth curve modelling and mixture modelling. For a GMM, we assume there are *K* latent classes in the population, and each class *k* has its own growth model with distinct parameters. Within each class *k*, the model for the serum creatinine response variable is as follows:

$$y_{ij}=x_{ij}\beta_{k}+z_{ij}u_{ki}+\epsilon_{kij}$$

where

$x_{ij}$
 and $z_{ij}$ are as defined previously.

$\beta_{k}$
 is the column vector of fixed-effects coefficients for class *k*.

$u_{ki}$
 is the column vector of random effects for the *i*th patient in class *k*.

$\epsilon_{kij}∼N(0,\sigma_{k}^{2})$
 is the residual error for the *i*th patient at the *j*th measurement point in class *k*.

We will employ a joint modelling framework to link the longitudinal serum creatinine trajectory to the time to event outcome. The longitudinal sub-models (mixed-effects model or GMM) will characterize the renal trajectory. The survival sub-model will account for the informative censoring caused by competing risks such as death and MACE.

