### Outcomes

The primary endpoint of the study will be worsening of renal function. Early detection or prediction of WRF provides an opportunity for intervention to prevent progression to renal failure and acute kidney injury (AKI) and potentially prevent hospitalization and death. Serum creatinine was selected as the primary biomarker for modelling. While a retrospective glomerular filtration rate (eGFR) recalculation using a single formula (CKD-EPI 2021) was a way of standardizing the historical data, we decided on raw serum creatinine. This approach avoids any bias. The raw serum creatinine allows an ML model to learn the effect of age and gender on renal trajectories directly from raw data rather than being constrained by fixed eGFR coefficients. In addition, a 12-month prediction period has been chosen to align with routine chronic disease monitoring intervals in primary care, thereby bridging the gap between acute injury (AKI) and long-term disease progression. Therefore, WRF is defined by primary care data if any of the following occur within 12 months: (i) 30% increase in serum creatinine or (ii) 26.5 µmol/L increase in serum creatinine.

Secondary outcomes will include hospitalization for AKI, major adverse cardiovascular events (MACE) and all-cause mortality. These outcomes are included specifically to consider competing risks and to recognize that patients with HF may experience cardiovascular events or death before renal monitoring.

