### Sample size

The sample size calculation for the statistical models was done in accordance with Riley *et al*. to ensure adequate performance and avoid overfitting based on the expected number of predictors and prevalence of outcomes.^27^ The calculation was based on an expected prevalence of outcome of ∼25%, approximately 100 candidate predictor parameters (including non-linearity) and a target reduction factor of 0.9. For the RNN-LSTM ML approach, at least 36 000 patients are required based on the number of network parameters, published precedents in similar studies, and practical feasibility. The sample size for ML models is still under active research.^28^

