### Outcome predictions

We have created an approach, which is described in Supplementary File  *S3*, to forecast a patient’s future serum creatinine trajectory. *Figure 3* shows the application of the statistical models in predicting future serum creatinine measurements. Predicted pathways (a) and (b) cross the WRF threshold within 12 months, while pathway (c) does not. By forecasting potential creatinine trajectories, we could construct an empirical cumulative distribution for the probability of WRF over time (*Figure 4*). Using the estimated joint model, we will make dynamic predictions for competing secondary outcomes by deriving cumulative event probabilities based on a patient’s observed serum creatinine process, covariate history, and outcome-free survival up to the current time. This will be achieved via Markov chain simulation (Metropolis-Hastings algorithm) and a Monte Carlo process.^34^

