**Figure 4 ztag055-F4:**
[figure not shown]
Probability distribution for WRF within 12 months from the current serum creatinine measurement point.

Secondary outcome risks will be assessed using (i) cause-specific Cox regression models with ridge penalization and (ii) Cox proportional hazard models to subsets of patients who remain in the risk set—i.e. those who have not experienced secondary outcomes or been censored before pre-specified landmark time points.^35^ Additionally, we will explore joint latent class model, where patients are assumed to belong to a single latent class, defining the association between the longitudinal and survival sub models.^36^

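### Non-fatal MACE and AKI admission are cast as competing risks although neither ends follow-up, and the landmark rule read literally leaves their survivors out of the all-cause mortality model

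*Protocol article*

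**What the plan says.** All references are to the protocol article.

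- **Participants.** Follow-up starts at heart failure onset and stops at the last practice data collection or at "the date that they transferred out of the practice, their date of death, or the end of the study, whichever happens first". MACE and AKI admission are not on that list.
- **Outcomes, primary.** "WRF is defined by primary care data if any of the following occur within 12 months": a 30% or a 26.5 µmol/L rise in creatinine. Rises after a MACE or an AKI admission are not excluded.
- **Outcomes, secondary.** "Secondary outcomes will include hospitalization for AKI, major adverse cardiovascular events (MACE) and all-cause mortality". On their purpose: "These outcomes are included specifically to consider competing risks".
- **Statistical modelling.** "The survival sub-model will account for the informative censoring caused by competing risks such as death and MACE".
- **Outcome predictions.** WRF probability is built from forecast creatinine trajectories. The secondary outcomes, called competing, are predicted from the joint model given the patient's creatinine process, "covariate history, and outcome-free survival up to the current time".
- **Outcome predictions, below Figure 4.** Secondary-outcome risks are assessed with cause-specific Cox models and with landmark Cox models. The landmark risk set is "those who have not experienced secondary outcomes or been censored before pre-specified landmark time points".

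**The concern.** A competing event makes the event of interest impossible. A censoring event ends observation. Death does both for WRF. A MACE that the patient survives does neither: under Participants the patient stays in the cohort, creatinine can still be measured, and WRF or death can still follow. An AKI admission is itself a renal event, of the kind that the Outcomes section hopes early detection of WRF will prevent, so it is an odd rival to WRF.

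The landmark rule turns this into a change of target. It refers to the secondary outcomes collectively, not to the outcome being modelled. A mortality model at a three-year landmark would then include only patients with no MACE and no AKI admission in those three years. That is mortality among patients who have so far had neither event, whereas the named outcome is mortality from all causes. The tool is meant for rolling prediction through follow-up, so patients with an intervening event will be among those needing a prediction.

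**Working it through.** **1. Sections side by side**

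| Event | Ends follow-up (Participants) | Prevents later WRF | Prevents later death | Role in the plan |
|---|---|---|---|---|
| Death | yes | yes | n/a | competing risk, informative censoring |
| Non-fatal MACE | no | no | no | competing risk, informative censoring |
| AKI admission | no | no | no | competing risk (Outcomes); not named in Statistical modelling, which gives examples only |

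The last two rows conflict with the follow-up rule. The article does not separate fatal from non-fatal MACE, and it describes no multistate or recurrent-event treatment. Predictors describes comorbidities as static and gives laboratory tests and medication as examples of dynamic predictors.

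**2. Landmark risk set (secondary outcomes)**

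The article states no figure to reproduce. Assume a constant non-fatal event hazard *l* = −ln(1 − *q*) for annual risk *q*. If mortality is unrelated to earlier events, the share of survivors removed by year *L* is 1 − (1 − *q*)^*L*.

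If mortality is *m* per year before the event and *ρm* after it, then among patients alive at *L*:
- event-free: *F* = exp(−(*m* + *l*)*L*)
- with an earlier event: *E* = *l*[exp(−*ρmL*) − exp(−(*m* + *l*)*L*)] / (*m* + *l* − *ρm*)
- share removed: *E*/(*E* + *F*)

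Example with *q* = 10%, *m* = 0.16, *ρ* = 3, *L* = 3: *l* = 0.1054, *F* = 0.451, *E* = 0.1054 × (0.2369 − 0.4511)/(0.2654 − 0.48) = 0.105, share = 0.105/0.556 = 19%.

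| Annual event risk (assumed) | 3 years, mortality unrelated | 3 years, *m* = 0.16, *ρ* = 3 | 5 years, mortality unrelated | 5 years, *m* = 0.16, *ρ* = 3 |
|---|---|---|---|---|
| 5% | 14% | 10% | 23% | 12% |
| 10% | 27% | 19% | 41% | 24% |
| 20% | 49% | 37% | 67% | 47% |

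The share depends strongly on the assumptions, but it grows with the landmark in every row.

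**3. WRF, only if observation stopped at the non-fatal event**

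Take 12-month WRF as 25%. Sample size is "based on an expected prevalence of outcome of" about 25%; reading that as 12-month WRF is an assumption. Let *h* be the WRF hazard before the event and *rh* after it, with *h* solved so that total WRF is 25%.
- WRF before the event: *h*/(*h* + *l*) × [1 − exp(−(*h* + *l*))]
- lost share: (0.25 − WRF before the event)/0.25

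Example with *q* = 10%, *r* = 2: *h* = 0.2748, *l* = 0.1054; WRF before the event = 0.7228 × 0.3163 = 0.2286; lost = 0.0214/0.25 = 8.6%.

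| Annual event risk | WRF before event, *r* = 1 to 3 | WRF events lost |
|---|---|---|
| 5% | 24.4% to 23.5% | 2.4% to 5.9% |
| 10% | 23.8% to 22.1% | 4.8% to 11.5% |
| 20% | 22.5% to 19.5% | 9.9% to 22.1% |

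If the event were treated as independent censoring instead, estimated 12-month WRF, 1 − exp(−*h*), would range from 25.0% (*r* = 1) down to 21.6% (*q* = 20%, *r* = 3).

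**The case against.** The best defence is that time to first event among AKI admission, MACE and death is a legitimate design. Its risk set is exactly the patients free of all three, and cause-specific Cox models are named. The landmark phrase might mean that design, or might mean each model's own outcome. The ambiguity is real, but the first-event reading does not rescue the plan: all-cause mortality is a named outcome in its own right, and a first-event analysis does not count deaths that follow a MACE.

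Three stronger readings are tempting, and the article does not support them.

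- **WRF is estimated in a depleted subset.** The explicit exclusion is written only for secondary-outcome models. WRF comes from forecast creatinine trajectories, and nowhere are values after a MACE said to be deleted. A joint model can also adjust in part for informative dropout, although if values did stop at MACE it would describe a trajectory without MACE.
- **The LSTM is judged on a different target.** The survival sub-model is attached only to the two statistical models, but the LSTM uses the same longitudinal data, and Model assessment applies the same measures to all three strategies. Different fitting does not imply different scoring.
- **Patients with past MACE or AKI get no valid prediction.** History of AKI and ischaemic heart disease are listed among the predictor factors, and laboratory values update at every measurement. The gap concerns events after the index date in the secondary-outcome models.

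It is also fair that every rate in the calculations is assumed, and that higher mortality after an event shrinks the landmark shares, as the table shows.

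**Conclusion.** The concern holds in limited form. Statistical modelling and Outcomes give MACE and AKI admission a role that the follow-up rule contradicts. Taken literally, the landmark rule makes the mortality model estimate something other than all-cause mortality in the cohort, in a subset that becomes more selected at later landmarks. This follows from the text and needs no assumed rate.

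The size cannot be fixed from the document. The landmark shares illustrate how selection grows and are not forecasts. The 2% to 22% loss of WRF events is doubly conditional: on literal censoring at MACE, which is not stated, and on assumed annual event rates of 5% to 20% with hazard ratios of 1 to 3. That the removed patients are at higher risk is a reasonable inference, not a documented figure.

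**What to change.** Reconcile Participants, Outcomes, Statistical modelling and Outcome predictions before any model is fitted:

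1. For WRF, name death as the competing (terminal) event. State that creatinine follow-up continues after a non-fatal MACE or an AKI admission.
2. Enter those non-fatal events as time-updated predictors, or as states in a multistate model.
3. Define each landmark risk set by outcome. Remove a patient only for death, for censoring or, in a first-event analysis, for an earlier event of that same type.
4. Reword the conditioning on outcome-free survival to match, saying which outcome is meant in each prediction.

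The cost is revised wording, a changed risk-set definition and slightly more modelling work. No new data are needed.
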